## Abstract

**Background:**

Vaccination has a huge public health impact. Maintaining vaccine coverage is key to avoid the devastating consequences of resurgence. In the Province of Québec, vaccine coverage in young children are sub-optimal, mostly due to ambivalence toward vaccine safety and efficacy. We previously conducted a regional study in the Québec’s Eastern Townships region, the PromoVac Study, to test a new educational intervention, based on motivational interviewing techniques, aimed at promoting infant vaccination. This first study evidenced that the intervention led to a marked increase in mothers’ intention to vaccinate, and vaccine coverage in their infants. The current study protocol aims at scaling up these results at a provincial level using a randomized controlled trial design.

**Methods:**

This pragmatic, randomized, controlled, parallel-group clinical trial will compare the effectiveness of the motivational interviewing to an educational intervention, including the distribution of an information flyer as standard of care on vaccination coverage in four maternity wards across the Province of Québec (PromovaQ). Adult mothers of children born in participating maternity wards were recruited between March 2014 and February 2015. Vaccination coverage will be assessed at 3-years of age, thus the trial is expected to be completed in March 2019. Statistical analyses will be conducted under the intention-to-treat principle. Vaccine coverage will be analyzed using Chi-squared distribution testing and logistic regression to identify determinant factors. Secondary outcomes will include vaccine hesitation and intention scores, mother’s knowledge, attitudes and beliefs about immunization, and psychosocial determinants of intention to vaccinate.

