## Methods/design

### Design

This pragmatic, unblinded, parallel, randomized, controlled study will compare the impact of a motivational interview (MI) vs the standard of care information leaflet provided to mother of infants born in the past 48 h. The trial recruitment period covered March 2014 to February 2015, with a final outcome measured in 3-year old children. Taking into account the time required to complete data collection and extraction from the appropriate national vaccination and health registries, this trial will be completed in March 2019. Randomization was conducted at the participant/maternal level, using a block size strategy (eight participants/block) to avoid bias. Randomization was stratified by site using a 1:1 allocation ratio to ensure proportionate allocation among sites. Random allocation was investigator-blinded using a web-based system (Dacima Software).

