### Study outcomes

The primary outcome will be vaccine coverage at 7 months. Secondary outcomes are: 1) vaccine status (complete, incomplete or non-vaccinated) at ages 3, 5, 13, 19, 24 and 36 months; 2) median vaccination age for vaccines recommended at 2, 4, 6, 12 and 24 months; 3) mean number of days under-immunized at 2, 4, 6, 12 and 24 months; 4) maternal intention to vaccinate pre- and post-intervention; 5) maternal vaccination hesitancy score pre- and post-intervention. Independent variables are maternal socio-demographic and clinical characteristics, the perceptions and opinions toward vaccination of families having received the MI-based intervention, and components of the composite model used for the study (Fig. 2).

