### Outcome measurements tools

Vaccine coverage will be calculated from data uploaded from the Eastern Townships public health vaccination registry, the provincial vaccination registry (2016 - onwards) and the postal survey of mothers of children born in Montreal-area maternity wards. To collect data on family beliefs, attitudes and intention to vaccinate, questionnaires were distributed to families pre- and post-intervention. The pre-intervention (Q1) and post-intervention (Q2) questionnaires were elaborated and built according to a composite model (Fig. 2) inspired from the Health Belief Model [38] and the Theory of Planned Behaviour [39]. Both questionnaires were self-administered and validated during the PromoVac study. Answers were provided according to a 4-category Likert scale. Q2 also collected data with respect to maternal satisfaction regarding the MI-based intervention received. Q2 was offered only to mothers having received the MI-based study intervention. Throughout the study, research assistants at each participating maternity kept a record of all implementation barriers and facilitators.

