### Sample size

The 2012 survey estimated vaccine coverage was 74% at 7 months for Québec infants [40]. Our hypothesis is that the intervention will improve vaccine coverage by a minimum of 5% raising it to 79% for mothers having received the MI-based intervention at the maternity ward. A total of 1128 participants are needed to detect a significant difference of 5% in vaccine coverage at 7 months of age, with a risk of error α = 0.05, a power of 80% and using a bilateral test. Factoring a 20% rate of attrition, notably for the Montreal-area for which there is no vaccination registry, a total of 2750 mothers were included in this study i.e. 625 from the Montreal-area and Québec city sites, and 875 from the Sherbrooke site, in order to compensate for follow-up losses at both Montreal-area sites.

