### Analytical statistical plan

Files containing vaccination data on participants and the questionnaires from each site will be sent to the Institut National de Santé Publique du Québec (INSPQ) for centralized data capture and analyses. Descriptive analyses of answers provided from each of the two study questionnaires will be performed. Primary analyses will be performed under intention to treat, whereas sensitivity analyses will include per protocol analyses. Frequencies and percentages will be presented as categorical variables. Means and standard deviations will be presented for normally-distributed continuous variables. Medians and interquartile ranges will be presented for abnormally-distributed continuous variables. Answers to the pre- and post-intervention questionnaires, notably the trans-theoretical stages of change model components, as well as the intention to vaccinate measured pre- and post-intervention will be compared using the McNemar’s test for categorical variable and Wilcoxon signed-rank test for continuous variable. Pre-intervention intention to vaccinate will then be dichotomized (“Certainly” answers, defined as certain, vs. “Probably”, “Probably not” and “Certainly not” answers, defined as uncertain) and compared by univariate analysis to the other variables as measured pre- and post-intervention. Categorical variables and vaccination intention will be compared using the Khi2 or Fisher exact test (expected frequency < 5). Normally-distributed continuous variables will be compared to intention to vaccinate using Student’s T-test and abnormally-distributed continuous variables will be compared to intention using the Mann-Whitney test. To identify the principal influencing factors on the “certain” intention to vaccinate, a multivariate logistic regression model with a step-by-step method will be used. To avoid co-linearity between the model’s independent variables, only those variables with a univariate *p* < 0,1 and a correlation coefficient < 0,6 (Pearson correlation, Spearman correlation) will be integrated into the multivariate logistic regression model. Co-linearity will be checked for the final model, and model fit will be assessed using the Akaike Information Criterion and the Hosmer and Lemeshow test. The vaccination status of the children will be compared between the intervention and the control groups. Missing data will be handled through multiple imputation techniques. All statistical will be 2-tailed and *p*-values of 0.05 or less will be considered significant.

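### The only test named for vaccine coverage ignores the site strata and the baseline intention score; using both is a modest, free gain in precision

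*Protocol article*

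**What the plan says.** The primary endpoint is fixed under Study outcomes: "The primary outcome will be vaccine coverage at 7 months". The only test tied to coverage stands in the abstract's Methods paragraph: "Vaccine coverage will be analyzed using Chi-squared distribution testing and logistic regression to identify determinant factors". The Analytical statistical plan section says no more about the arm comparison than "The vaccination status of the children will be compared between the intervention and the control groups", with no test, stratum, covariate or effect measure. The regression that section does describe in detail ("a multivariate logistic regression model with a step-by-step method will be used") has certain intention to vaccinate as its outcome, not coverage by arm.

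On the design side, the Design section states: "Randomization was stratified by site using a 1:1 allocation ratio to ensure proportionate allocation among sites". Coverage data come from registries for the Eastern Townships and Québec City and from a postal survey for Montreal (Outcome measurements tools; Discussion). The Sample size section expects attrition of 20%, mainly in Montreal, and enlarges one site for that reason: "875 from the Sherbrooke site, in order to compensate for follow-up losses at both Montreal-area sites".

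On baseline data, Outcome measurements tools states: "To collect data on family beliefs, attitudes and intention to vaccinate, questionnaires were distributed to families pre- and post-intervention". It then adds: "Q2 was offered only to mothers having received the MI-based study intervention". Only the second questionnaire is restricted to one arm, which implies that Q1 exists in both. The Analytical statistical plan section already defines a certain/uncertain split of the Q1 intention item. It also plans intention to treat and multiple imputation, without naming the imputation variables.

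**The concern.** When randomization is stratified, the arm difference varies less from one randomization to another than an unstratified standard error assumes. A test that ignores the strata therefore uses a standard error that is somewhat too large whenever coverage differs between sites. A pre-intervention measure of intention may predict coverage more strongly than site does, and leaving it out gives up precision in the same way.

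The trial has little power to spare: with 20% attrition it has about 79% (see the working). A second question is whether heavier loss in Montreal, where coverage is collected by post, could distort a comparison that ignores site.

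**Working it through.** **1. The plan's own figure.** Inputs from Sample size: 74% versus 79%, two-sided α = 0.05, power 80%. The pooled-variance formula is n per arm = [1.960·√(2·0.765·0.235) + 0.8416·√(0.74·0.26 + 0.79·0.21)]² / 0.05². With numbers: (1.1752 + 0.5038)² / 0.0025 = 1127.6, so 1128. The figure is reproduced, but per arm; its wording as a total is a separate matter. With 20% loss, 2750 × 0.8 / 2 = 1100 per arm remain, which gives 79.0% power.

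**2. Cost of ignoring site, by hand.** Site sizes from Sample size: 625, 625, 625, 875 (sum 2750). Site coverage is not given, so two spreads are assumed, in the order Montreal, Montreal, Québec City, Sherbrooke. The variance ratio is 1 − (between-site variance) / [p(1 − p)].

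| Assumed coverage | Overall p | Between-site variance | p(1 − p) | Ratio |
|---|---|---|---|---|
| 70/70/76/78% | 0.739 | 0.00133 | 0.1928 | 0.993 |
| 62/66/80/84% | 0.740 | 0.00873 | 0.1924 | 0.955 |

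For the wide spread, √0.955 = 0.977. The plain test's true type I error is then 2·[1 − Φ(1.960/0.977)] = 4.5%. Its power is Φ(0.8416/0.977) = 80.5%, against Φ(2.8016/0.977 − 1.960) = 81.8% for the stratified test, a gain of 1.2 points before rounding. For the moderate spread the gain is about 0.2 points and the type I error 4.9%.

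**3. Simulation, adding baseline intention.** Settings: stated site sizes, 18% loss at every site (about 1128 analysed per arm), overall 74% versus 79%, and 4000 to 6000 runs per scenario. Assumed: 60% of mothers certain, and an intention-coverage odds ratio (OR) of 2, 4 or 8. Power of chi-squared → Cochran-Mantel-Haenszel (CMH) by site → CMH by site and intention:

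| Site spread | OR 2 | OR 4 | OR 8 |
|---|---|---|---|
| none | 80.8 → 80.8 → 81.4% | 79.6 → 79.7 → 82.5% | 80.1 → 80.1 → 86.8% |
| moderate | 80.5 → 80.9 → 81.5% | 81.1 → 81.1 → 84.3% | 80.3 → 80.5 → 86.5% |
| wide | 79.8 → 81.6 → 82.4% | 79.5 → 81.0 → 84.3% | 80.9 → 82.1 → 88.3% |

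The gain from site alone is 0 to about 2 points. The total gain is 0.6 to 2.6 points at OR 2, 3 to 5 at OR 4, and 6 to 7 at OR 8. Under the null the plain test rejected in 3.9% to 5.5% of runs. At 4000 runs the Monte Carlo standard error is √(0.05·0.95/4000) = 0.34 points, so this is nominal to slightly conservative.

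**4. Loss by site, equal in both arms.** With 40% loss in Montreal and 2% elsewhere, bias under the null was 0.01 points and type I error 4.4% to 4.8%.

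**5. Loss in Montreal that also differs by arm (assumed, complete cases).** Each arm has 625 Montreal and 750 other infants; at 2% loss, 735 of the others are observed. With Montreal loss of 45% in control and 35% in intervention, Montreal's share of observed infants is 343.75/1078.75 = 31.9% versus 406.25/1141.25 = 35.6%. The wide spread puts Montreal 18.3 points below the other sites, so the bias is −3.73% × 18.3 = −0.68 points (simulated −0.66). Across the two spreads and two loss patterns (45% versus 35%; 50% versus 30%), the simulated bias was −0.2 to −1.4 points, with type I error of 5.3% to 11%. CMH by site was unbiased, with type I error of 4.7% to 5.2%.

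**The case against.** The strongest reply has four parts.

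- **The chi-squared test is not called primary.** The sentence is an abstract's summary, it does not exclude an adjusted analysis, and the full analysis plan is not shown. This stands as a caution. Still, the article does name a method for coverage and gives logistic regression a different job, so the point concerns a stated choice and not a missing detail.
- **A chi-squared test is valid.** This stands in full. A reader might infer an inflated false-positive rate; with equal loss across arms, the test errs slightly the other way.
- **Site-related loss is not simply ignored.** A reader might infer that heavy Montreal loss biases the result. The documents do not support that: loss that differs by site but not by arm leaves the comparison unbiased, and no section suggests that Montreal response differs by arm. The bias in step 5 also assumes a complete-case analysis, whereas the article plans multiple imputation under intention to treat. What remains is that neither the comparison nor the imputation is stated to contain site.
- **The precision gain rests on assumptions.** This stands. The documents give neither coverage by site nor the link between Q1 intention and coverage, and at an odds ratio of 2 the total gain is mostly 0.6 to 1 point.

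Nor would stratifying by site repair response that depends on vaccination status within Montreal.

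**Conclusion.** The point holds as a free improvement. The only analysis named for coverage uses neither the stratification factor nor the pre-intervention intention score. The result is a valid, slightly conservative test with some precision given up: about 0 to 2 power points for site alone, and about 0.6 to 7 points for site plus Q1 intention over assumed odds ratios of 2 to 8. These sizes depend on assumed site coverage, an assumed 60% of certain mothers and the assumed odds ratios, and are illustrative.

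It would go too far to call the planned test invalid, or to say that follow-up loss has been left to bias the result. Bias needs Montreal response to differ by arm, and multiple imputation addresses that if arm and site are in its model and response within site and arm does not depend on vaccination status beyond the variables included.

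**What to change.** 1. Name one primary analysis of 7-month coverage. Either use a site-stratified comparison (CMH test, with the stratified risk difference), or a logistic model with arm, site and dichotomized Q1 intention, reported as a marginal risk difference with 95% CI. A risk difference with its standard error is also easy to combine across imputed data sets.
2. Put arm, site and Q1 intention in the imputation model.
3. Keep the crude chi-squared test as supportive and show the effect by site.
4. Before using Q1 as a covariate, confirm that it was collected in both arms and completed before the mother knew her allocation. The article implies the first and does not state the second. If either fails, adjust for site alone.

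The cost is wording in the analysis plan, dated before outcomes are linked to allocation. No new data are needed, provided Q1 passes the check in item 4.

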**Discussion:**

In the case results of this Provincial RCT be confirmed, serious consideration should then be given by Ministry of Health authorities to the possible implementation of MI-based strategies across provincial maternity wards. To ensure adequate input and secure implementation, study design and results will be reviewed with relevant stakeholders, including the children’s families, and provincial and regional decision-makers. Results will be adapted and shared with all stakeholders.

**Trial registration:**

ClinicalTrials.gov NCT02666872 (Retrospectively registered as January 28, 2016).

## Background

Vaccination has successfully curbed the mortality and morbidity of numerous vaccine-preventable diseases [1]. To keep the incidence of such diseases in check, high levels of vaccine coverage must be maintained, including among children who are most vulnerable. Although vaccine coverage in young children is high in the Province of Québec (Canada), levels are sub-optimal relative to provincial public health program targets. For instance, in 2014, complete vaccination coverage at age 2 years was 71% (85% if excluding rotavirus vaccine), compared to the 95% target [2]. Although the prevalence of most vaccine-preventable diseases remains currently low in the Province of Québec, the transmission of certain vaccine-preventable diseases proceeds uninterrupted. A decline in vaccine coverage could therefore lead to resurgence of currently controlled vaccine-preventable diseases. As an example, a measles outbreak that occurred in the Province of Québec in 2011 resulted in identification of 750 cases, mainly among non-fully immunized children and adolescents [3].

In addition, beyond sub-optimal vaccine coverage, another important issue is off-schedule immunization [4–7]. Delay in the 2-month vaccines was significantly associated with incomplete vaccine coverage at 15 and 24 months [4–7]. One consensus reached by Canadian experts is that late vaccination is defined by a one-month delay past the recommended schedule [8]. In the Province of Québec, late-vaccination management indicators were introduced in 2006 to collect data on late immunization at one week, two weeks, and one month passed the scheduled date for vaccination [9]. Previous surveys of vaccine coverage for 1- and 2-year-old children showed that only 17 to 36% of children aged 24 months had received all of their vaccines within one month of the recommended age [4, 10, 11].

Public health targets for vaccine coverage remain elusive and the persistence of late vaccination are both explained, in parts, by a lack of confidence on the part of the public. As it turns out, vaccination is currently a victim of its own past success. Indeed, the fear associated to vaccine safety has risen steadily among the population as its level of exposure to vaccine-preventable diseases has fallen [12, 13] . Numerous studies report that nearly one third of parents are currently hesitant toward vaccination, [14–19] an often strongly held viewpoint fueled by recent history controversies and media coverage [20].

Vaccine hesitancy and acceptance are intertwined concepts. The World Health Organization defines vaccine hesitancy as the “delay in acceptance or refusal of vaccines, despite availability of vaccine services” [21, 22]. A variety of educational methods, mostly based on providing parents with factual information, have been deployed to address vaccine hesitancy. However, none has as of yet proven effectiveness [23]. A recent Cochrane review of qualitative evidence, assessing parents’ views and experiences of communication about routine childhood vaccination, showed that parents required more information than what they were actually receiving and that simple, context-specific facts should be provided in a timely-manner by a trusty health worker [24]. The take-home message is that while parents want more information, traditional educational methods currently fail to meet their needs according to the literature. This begs the following question: how do we overcome the challenge of providing adapted factual information on vaccination to parents?

One possible approach, originally developed in the context of substance abuse, is the motivational interview (MI). MI has been used to elicit health-related behavioral changes in nutrition, physical activity and smoking [25–28]. MI is basically a patient-oriented communication strategy, used to elicit personal, internal motivation to attitude changes by exploring and solving inherent ambivalence [29]. Our group successfully adapted this approach to develop the PromoVac vaccination promotion program. PromoVac is offered to mothers directly at the maternity wards and is closely tailored to mother’ knowledge and beliefs. The PromoVac regional cohort observational study enrolled 1128 families at the CIUSSSE-CHUS (Centre intégré Universitaire de Santé et de Services Sociaux de l’EStrie – Centre Hospitalier Universitaire de Sherbrooke) maternity ward. Results demonstrated the feasibility and efficacy of the PromoVac MI-based educational intervention to promote both vaccination intention among mothers and vaccine coverage among infants [30, 31]. Results obtained from the PromoVac regional study support a larger, multicenter, randomized controlled trial taking into account the diversity of the Province of Québec’s population.

### Hypothesis

Our working hypothesis is that a vaccination promotion program based on a standardized, MI-based information session held directly at the maternity ward with mothers will increase vaccine coverage of infants in the Province of Québec.

### Objectives

The primary objective is to compare infants’ vaccine coverage at 7 months of age whose mothers, upon recruitment at the maternity ward, were randomized to receive the vaccination promotion study intervention or the standard educational leaflet. The secondary objectives are to compare: 1) infants’ vaccine coverage status (complete, incomplete or not vaccinated) at 3, 5, 13, 19, 24 and 36 months of age; 2) infants’ median age at vaccination for vaccines recommended at 2, 4, 6, 12 and 24 months; 3) mothers’ pre- and post-intervention intention to vaccinate; 4) mothers’ pre- and post-intervention vaccination hesitancy score; 5) maternal’ knowledge, attitudes, beliefs and intention to vaccinate. We also aim to identify intervention implementation obstacles, barriers and facilitators in maternity wards.

## Methods/design

### Design

This pragmatic, unblinded, parallel, randomized, controlled study will compare the impact of a motivational interview (MI) vs the standard of care information leaflet provided to mother of infants born in the past 48 h. The trial recruitment period covered March 2014 to February 2015, with a final outcome measured in 3-year old children. Taking into account the time required to complete data collection and extraction from the appropriate national vaccination and health registries, this trial will be completed in March 2019. Randomization was conducted at the participant/maternal level, using a block size strategy (eight participants/block) to avoid bias. Randomization was stratified by site using a 1:1 allocation ratio to ensure proportionate allocation among sites. Random allocation was investigator-blinded using a web-based system (Dacima Software).

